# Bedside Ultrasound Conducted in Kids with distal upper Limb fractures in the Emergency Department (BUCKLED): a protocol for an open-label non-inferiority diagnostic randomised controlled trial

**DOI:** 10.1186/s13063-021-05239-z

**Published:** 2021-04-14

**Keywords:** Ultrasound, Bedside ultrasound, Point-of-care ultrasound, X-ray, Radiography, Forearm, Distal forearm, Fractures, Buckle fracture, Diagnostic imaging

## Abstract

**Background:**

Children frequently present to the emergency department (ED) with forearm injuries and often have x-rays to determine if there is a fracture. Bedside ultrasound, also known as point-of-care ultrasound (POCUS), is an alternative diagnostic test used to rapidly diagnose a fracture at the time of examination, without exposing children to ionising radiation. Prospective studies have demonstrated high agreement between POCUS and x-ray findings. However, whether the initial imaging modality affects the patient’s medium-term physical function is unknown.

**Methods:**

This is a multicentre, open-label, non-inferiority randomised controlled trial conducted in Australian EDs. Recruitment will continue until 112 children with distal forearm injuries (including 48 buckle fractures) per trial arm have achieved the primary outcome measure. Patients aged 5–15 years presenting with an isolated, acute, clinically non-angulated, distal forearm injury with suspected fracture will have their initial diagnostic approach randomised to either POCUS, performed by a credentialled practitioner, or x-ray imaging. If a cortical breach fracture is identified on POCUS, the patient will receive x-rays and have usual care. If a buckle fracture is identified, the patient will have their forearm placed in a splint and be discharged home. Patients will be followed up at 1, 4 and 8 weeks. The primary outcome is upper limb physical function at 4 weeks, as determined by the Pediatric Upper Extremity Short Patient-Reported Outcomes Measurement Information System (PROMIS) tool. Secondary outcomes include healthcare costs, satisfaction, pain, complications, rates of imaging, ED length of stay and diagnostic accuracy.

**Discussion:**

If POCUS is non-inferior to x-ray in terms of patient’s medium-term physical function, it may have an effect on overall health care resource use, including the number of x-ray performed and earlier ED discharge. Although prospective studies have confirmed the accuracy of POCUS, this will be the first RCT to assess non-inferiority of functional outcomes of POCUS to diagnose non-angulated paediatric distal forearm injuries, compared to x-ray. POCUS may be of particular importance in settings where access to x-ray imaging can be limited either during or after-hours, as it can aid the triaging and management of patients.

**Trial registration:**

Prospectively registered with the ANZCTR on 29 May 2020 (ACTRN12620000637943).

## Introduction

### Background and rationale

Forearm fractures account for almost 2% of children presenting to the emergency department (ED) in Australasia and are the second most common reason for presentation of children aged 10–14 years [1]. They represent about one third of all fractures in children [2], are mainly distal and usually occur after a fall [3]. Many are diagnosed as buckle (torus) fractures, which are unique to children due to their malleable cortex within a strong periosteum [4]. Unlike other paediatric fracture types of the distal forearm, such as bowing, greenstick, complete or physeal fractures [5], patients with buckle fractures can be consistently discharged with a wrist splint with no routine requirement for further imaging or follow-up [6].

The current reference standard to diagnose a distal forearm fracture is 2-view x-ray [7]. These x-rays convey a small dose of ionising radiation, which should be minimised where possible in the paediatric population [8]. Bedside ultrasound, otherwise known as point-of-care ultrasound (POCUS), a portable form of non-ionising imaging conducted at the patient bedside [9], has the potential to avoid unnecessary x-ray imaging in children with clinically non-angulated distal forearm fractures [10], thereby supporting the ‘as low as reasonably achievable’ (ALARA) principle [11]. POCUS has been proposed as a potential alternative to x-rays to diagnose non-angulated paediatric distal forearm fractures. Systematic reviews of diagnostic studies have found POCUS is both highly sensitive and specific but studies were heterogeneous, with a mixture of users and techniques [12–14].

POCUS could potentially be used as a screening tool to determine the presence and type of fracture [10, 15]. Patients without any fracture or with only a buckle fracture can be conservatively managed akin to soft tissue injuries [6]. However, patients with a cortical breach fracture require x-rays to determine the extent of injury, management and follow-up. If patients with either no fracture or with only a buckle fracture can be reliably distinguished from a cortical breach fracture using POCUS, x-rays can be avoided, with potential favourable effects on costs for the patient and healthcare system [16]. Such process and economic outcome benefits would be of interest if the initial diagnostic approach using POCUS would lead to non-inferior patient-centred outcomes. To date, no randomised controlled trial (RCT) has compared POCUS versus x-ray as the initial diagnostic approach in terms of functional outcomes [12–14].

### Objectives

The primary objective of this trial is to assess whether, in children presenting to ED with distal forearm fractures, initial diagnostic imaging modality (POCUS compared to x-ray) affects functional upper limb outcomes. A secondary objective includes a health economic analysis to determine the cost-effectiveness of POCUS compared to x-ray as the initial imaging. We hypothesise that when POCUS, instead of x-ray, is used as the initial diagnostic tool for paediatric distal forearm fractures, upper limb physical function is non-inferior at 28 days post injury, with an overall reduction in x-rays and costs, without missing any clinically significant fractures.

### Trial design

This is a multicentre, open-label, non-inferiority RCT comparing paediatric clinically non-angulated distal forearm injuries by initial diagnostic imaging modality (POCUS to x-ray) to assess functional upper limb outcomes. The protocol adheres to the Standard Protocol Items: Recommendations for Interventional Trials (SPIRIT) Statement.

## Methods: participants, interventions and outcomes

### Study setting

The trial will be conducted across participating hospitals in Queensland, Australia. The participating hospitals will include both tertiary and non-tertiary centres, as well as a mixture of dedicated paediatric EDs and EDs with both adult and paediatric presentations.

### Eligibility criteria

The trial will recruit children aged between 5 and 15 years (i.e. up to 15 years and 364 days) with an isolated, acute, clinically non-angulated, distal forearm injury who are being further evaluated for a suspected fracture with imaging. The population of children between the ages of 5 and 15 years was chosen as the children within this age range can all sustain buckle fractures [17]. Patients with additional injuries deemed to require imaging, including midshaft forearm, proximal forearm, scaphoid or elbow tenderness, will be excluded. Patients will need to able to attend follow-up, if required, ideally living within a ~ 50-km radius of the enrolling hospital and have telephone and Internet access. See Table 1 for full inclusion and exclusion criteria.

**Table 1 Tab1:** Inclusion and exclusion criteria

Inclusion criteria	
• Child age 5–15 years *with*	
• Distal forearm injury *and*	
• Can attend any follow-up	
Exclusion criteria	
• Obvious angulation or deformity (soft tissue swelling allowed)	
• Injury sustained > 48 h prior	
• External x-rays already performed	
• Compound/open fracture (including concern for foreign body)	
• Neurovascular compromise	
• Known bone disease (e.g. osteogenesis imperfecta)	
• Suspicion of non-accidental injury	
• Additional injuries requiring x-rays (e.g. elbow, scaphoid)	
• Congenital forearm malformation (e.g. radius hypoplasia)	
• No credentialled clinician available to perform scan	
• Significant developmental delay or behavioural difficulties prohibiting accurate clinical assessment	

### Consent

Potentially eligible patients will be identified by nursing staff at triage with subsequent review by a credentialed clinician to examine patients and confirm final eligibility according to inclusion and exclusion criteria. Informed consent will be obtained from the legal guardian, hereafter referred to as the parent, after they have reviewed an information sheet. This is supplemented by an online video recording, with parents and/or participants having had the opportunity to ask any questions they need to. After fulfilment of written informed consent requirements, baseline data will be collected prior to randomisation.

### Interventions

Participants will be allocated to an initial diagnostic imaging modality of POCUS or x-ray. POCUS was chosen as the intervention for this trial as, for paediatric distal forearm fractures, it is non-invasive, accurate and well-tolerated; does not emit ionising radiation; and is preferred by patients [10]. X-ray was chosen as the control comparator as not only is it a pragmatic reference standard, but also it currently guides routine practice in the ED and subsequent standard outpatient follow-up. MRI was considered costly and impractical to use as the reference standard in an acute setting and may detect clinically irrelevant fractures or bone contusions, and CT would expose patients to unnecessary ionising radiation [18].

#### Pocus

Eligible patients randomised to POCUS will have imaging performed by a health practitioner (nurse, doctor or allied health professional) who has undergone training and credentialing. Credentialing consists of a 2-h simulated training package with a phantom arm model [16], followed by proctored scanning, the collection of a logbook of scans demonstrating a total of 20 patients with a mixture of at least 10 buckle or cortical breach fractures, image interpretation from a bank of case examples and a final observed assessment. A modified 6-view forearm POCUS protocol will be conducted, whereby the distal radius and ulna are interrogated on their dorsal, lateral and volar aspects with a high frequency linear probe in a longitudinal axis with the probe marker orientated distally [10]. Secondary signs will also be assessed (Table 2), which includes the pronator quadratus haematoma sign [19]. Patients will be provided with analgesia as required and rest their forearm, ideally on a pillow, during the procedure. Pain will be minimised by use of gel and minimal probe pressure. The final image(s) will be prospectively labelled with the overall forearm diagnosis, being as specific as possible for the cortical breach subtype.

**Table 2 Tab2:** Criteria for consideration of x-ray imaging after POCUS

POCUS Primary sign	
• Identification of a cortical breach fracture (apart from an isolated ulna styloid fracture or non-displaced, non-angulated ulna metaphyseal fracture)	
POCUS Secondary signs:	
• Buckle fracture < 1 cm from physis	
• Pronator quadratus haematoma present (i.e. positive fat pad sign)	
• Angulation greater than ~ 5 degrees (visually angulated)	
• Physis widened or narrowed	
• Periosteal haematoma	
Clinical basis	
• Clinical suspicion, despite normal POCUS findings e.g. ‘pain out of proportion’ as per clinician judgement	

Patients will receive an overall forearm diagnosis based on the POCUS findings and be classified into 3 fracture categories: ‘no’, ‘buckle’ or ‘other’. A ‘buckle’ fracture is defined as an inward or outward deformation of bone cortex without breach. The ‘other’ fracture group will consist of any fracture with a cortical breach identified using POCUS. A cortical breach is defined as a break, step or gap in the bone cortex. Both the radius and ulna bones will be individually classified, with the overall forearm classification based on the overarching fracture that determined the management of the patient (Table 3). If classified as ‘other’ fracture on POCUS, they will receive an x-ray and be managed on that basis. If either ‘no’ or ‘buckle’ fracture is identified on POCUS, the patient will not receive an x-ray prior to discharge. Ulna styloid, or non-displaced, non-angulated ulna metaphyseal fractures will be considered clinically insignificant and can be managed conservatively in a wrist splint. Both the x-ray and POCUS images will be later reviewed for correct fracture classification and clinical relevance by an expert panel.

**Table 3 Tab3:** Overall fracture diagnosis group classifications

‘No’ fracture	
• No fracture of the radius or ulna	
‘Buckle’ fracture	
• Buckle fracture of the distal third radius, with or without:	
- Ulna styloid fracture	
- Ulna metaphysis non-displaced/non-angulated buckle or cortical breach fracture.	
• Isolated buckle fracture of the distal third ulna	
‘Other’ fracture	
• Cortical breach fracture of the distal third radius (including greenstick, complete or physeal), with or without any ulna fracture type	
• Any isolated displaced/angulated cortical breach fracture of the ulna metaphysis	
• Fractures at other locations, e.g. proximal radius, scaphoid	
• Bowing fractures of the radius and/or ulna with or without any other fracture type	

#### X-ray

Eligible patients randomised to x-ray will have a minimum of 2 views performed by a radiographer and reported by a radiologist or radiology trainee, with both groups masked to the initial diagnostic allocation and any POCUS findings. X-ray imaging will be interpreted by the treating clinician and classified into 3 fracture categories, as per the POCUS trial arm (‘no’/‘buckle’/‘other’). A ‘buckle’ fracture is defined as an inward or outward deformation of bone cortex without breach. The ‘other’ fracture group will consist of cortical breach fracture types, including greenstick (uni-cortical), complete (bi-cortical) or physeal (Salter-Harris), and also bowing fractures and fractures at other sites (e.g. scaphoid) if incidentally not excluded on physical examination. A cortical breach is defined as a break, step or gap in the bone cortex.

#### Management

The management principles will be the same for both the POCUS and x-ray trial arms. The ‘no’ fracture group will be conservatively managed at the clinician’s discretion, as documented in the medical record. The ‘buckle’ fracture group will be managed in a wrist splint and the ‘other’ fracture group will be managed with intervention (manipulation, reduction and/or surgery) and immobilisation in a plaster cast or equivalent as required.

All patients who are diagnosed as either ‘no’ or ‘buckle’ fracture in either study arm (POCUS or x-ray) will be given a tentative appointment for ED clinical review in approximately 1 week (5–7-day convenience window) at the site they were originally managed. The parent will be contacted with a standard script prior to the appointment and the review will be cancelled if no longer required due to clinical improvement. If a clinical review is attended, the parent and practitioner will prospectively document whether they believe x-rays are required. X-rays will then only be performed if indicated by clinical suspicion, unless the parent decides against it and this is supported by the reviewing practitioner. Patients will then receive usual care as per x-ray findings, with the orthopaedic service consulted for any displaced or angulated fractures.

#### Criteria for discontinuing or modifying allocated interventions

X-ray will be performed as per usual practice, with views limited by patient tolerability. Inadequate views may require repeating, as per clinician judgement. Although it is unusual to be unable to obtain x-rays, if this occurs, reasons will be documented. POCUS will be discontinued if the patient experiences undue distress or excessive pain whilst POCUS is performed, or if adequate images are unable to be obtained, and will receive x-rays instead. If classified as ‘other’ fracture on POCUS, such as identification of a cortical breach, they will receive an x-ray and be managed accordingly. Patients may also receive x-rays based on secondary signs of a cortical breach fracture detected on POCUS or ‘pain out of proportion’ as per treating clinician judgement. Full criteria for x-ray imaging consideration after POCUS are listed in Table 2. Patients who subsequently receive x-rays will receive routine cares based on its findings.

Once the initial diagnostic test (POCUS or x-ray) has been conducted, the intervention will be considered complete. Patients will receive analgesia as required, which will be documented for comparison between diagnostic arms and subgroups. The trial has been designed to safeguard against any clinically significant fractures being missed in either study arm. The extended POCUS protocol is designed to utilise secondary signs, such as the pronator quadratus haematoma sign, which shows promise as an additional measure to avoid missing any cortical breach fractures [19]. Furthermore, the follow-up review, if required, is an appropriate timeframe to intervene for any missed fractures. All patients with a displaced or angulated fracture of significance will receive orthopaedic specialist care, including during and after the trial. Any deviation from the protocol will be noted, specifically if this changed fracture management.

### Outcomes

#### Trial endpoints

The primary outcome is upper limb physical function at 4 weeks (28 days ±3 days) as measured by the validated Pediatric Upper Extremity Short Patient-Reported Outcomes Measurement Information System (PROMIS) tool. This timeframe was chosen, as patients with buckle fractures and soft tissue injuries should have regained normal physical function by this time, compared with cortical breach fractures. Provided there are no re-injuries, 8 weeks is an accepted time frame for fracture healing in children, with recovery of function within 3–4 weeks for children with distal forearm buckle fractures [20]. The earlier follow-up period as the primary outcome is designed to detect any difference of arm function between diagnostic groups, with complications being a secondary outcome.

Health economic analysis will be conducted to determine the cost-effectiveness of POCUS compared to x-ray with the main outcome being the incremental cost per quality adjusted life year from both a health care sector perspective and broader societal perspective. Refer to Table 4 for complete primary and secondary outcomes. Data will be collected at designated time points across an 8-week period (Fig. 1, SPIRIT participant timeline).

**Table 4 Tab4:** Outcome measures for POCUS and x-ray trial arms

Primary outcome measure:	
• Physical function of injured upper limb at 4 weeks (28 ± 3 days), as determined by the PROMIS tool.	
Secondary outcome measures:	
• Direct and indirect health care costs (healthcare provider visits, days off work/school)	
• Health related quality of life (QOL), as determined by the CHU9D	
• Satisfaction score (patient and parent)	
• Patient pain score measured using the FPSR	
• Rates of complications (alternate fracture diagnosed, poor fracture healing)	
• Rates of x-ray and other imaging (particularly the ‘no’ and ‘buckle’ fracture groups)	
• ED length of stay (triage to ED discharge)	
• Treatment time (clinician review to ED discharge)	
• Diagnostic accuracy of POCUS, including secondary signs, and x-ray	

Key: *PROMIS* Pediatric Upper Extremity Short Patient-Reported Outcomes Measurement Information System, *CHU9D* Child Health Utility 9D, *FPSR* Faces Pain Score Revised

**Fig. 1 Fig1:**
[figure not shown]
Participant timeline (SPIRIT format)

#### Sample size

Sample size calculations were based on a non-inferiority hypothesis comparing POCUS with x-ray (routine care) for the primary outcome of upper limb function assessed using the PROMIS score at 4 weeks. Previous studies suggest the true between-group difference was assumed to be zero with the non-inferiority margin defined as an absolute difference of 5 points and the standard deviation of PROMIS assumed to be 11.5 points [21–23]. To achieve 90% power with a one-sided α of 0.025, we require primary outcome data for 224 children (112 per arm).

A key secondary endpoint is to assess the non-inferiority of POCUS compared with x-ray as the initial imaging strategy for children who are later confirmed by the expert panel to have buckle fractures. Previous studies suggest that the standard deviation of PROMIS for children with buckle fractures is approximately 7.5 points [21–23]. Assuming the true between-group difference is 0 and defining the non-inferiority margin as 5 points, then with 90% power and one-sided *α* = 0.025, we require primary outcome data on 96 children with buckle fractures (48 per arm). We assume 35–45% of participants will be diagnosed with buckle fractures by the expert panel.

Recruitment will continue until primary outcome data has been collected on both at least 112 children per arm and at least 48 buckle fractures per arm. Allowing for approximately 25% attrition and variation in buckle fracture prevalence, we expect to recruit up to 300 patients to achieve the required sample size.

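### The forecast of up to 300 recruits does not fit the plan's own attrition and buckle-prevalence assumptions: the buckle target needs about 285 to 366 in expectation

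*Protocol article*

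**What the plan says.** All the inputs are in the Sample size section of the protocol article.

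- **Overall target:** "To achieve 90% power with a one-sided α of 0.025, we require primary outcome data for 224 children (112 per arm"), with a margin of 5 points, a true difference of zero and an SD of 11.5.
- **Buckle target:** for the key secondary comparison, "we require primary outcome data on 96 children with buckle fractures (48 per arm"), using an SD of 7.5 and the same margin, power and one-sided α.
- **Prevalence:** "We assume 35–45% of participants will be diagnosed with buckle fractures by the expert panel".
- **Stopping rule:** recruitment goes on until outcome data exist for both minimum counts in each arm. The Abstract gives the same pair of counts: "Recruitment will continue until 112 children with distal forearm injuries (including 48 buckle fractures) per trial arm".
- **Forecast:** "Allowing for approximately 25% attrition and variation in buckle fracture prevalence, we expect to recruit up to 300 patients", which the sentence says is enough for the required sample size.

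The Randomisation section gives 1:1 allocation.

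**The concern.** The forecast sentence claims to cover two things, loss to follow-up and uncertainty about how many children have a buckle fracture. Yet inflating the overall target of 224 for 25% loss already gives 299, which leaves almost nothing of the 300 for a low buckle prevalence. With two minimum counts, the binding one is whichever fills more slowly. The article never shows which one that is across its assumed 35–45%.

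At stake is the credibility of the only recruitment total in the article. A reader who takes 300 at face value would expect the key secondary comparison to be fully populated at that point. If the buckle count binds, the trial will have to go beyond 300 to satisfy its own rule.

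**Working it through.** **1. Reproduce the per-arm targets.** For non-inferiority of means with a true difference of zero, n per arm = 2(z₀.₉₇₅ + z₀.₉₀)² SD² / margin².

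- Overall: 2(1.96 + 1.2816)² × 11.5² / 5² = 111.2, so 112.
- Buckle: 2(1.96 + 1.2816)² × 7.5² / 5² = 47.3, so 48.

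Both match the article. (Calculations based on the t distribution give 113 and 49, an immaterial difference.)

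**2. Find what reproduces 300.** Inflating the overall target for 25% loss gives 224 / 0.75 = 298.7, so 299. A different route gives exactly 300: 96 / 0.40 = 240 evaluable children, then 240 × 1.25 = 300. The second route is not the right inflation for a 25% loss, which requires division by 0.75 (240 / 0.75 = 320). The article shows no derivation, so either route is possible.

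**3. Find the break-even prevalence for 300.** Evaluable children: 300 × 0.75 = 225. Prevalence needed for 96 expected buckle fractures: 96 / 225 = 42.7%. The share of the 35–45% range below this is (42.67 − 35) / 10 = 77%, which includes the midpoint of 40%.

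**4. Compute recruits needed, yield and chance of success.**

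- Recruits needed in expectation = 96 / (p × 0.75).
- Expected evaluable buckle fractures from 300 = 225p.
- Chance that both arms reach 48 with 150 randomised per arm = P(Bin(150, 0.75p) ≥ 48)².

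| Prevalence p | Recruits needed (expected) | Buckle fractures from 300 (per arm) | Chance that one arm reaches 48 | Chance that both reach 48 |
|---|---|---|---|---|
| 35% | 365.7, so 366 | 78.75 (39.4) | 6.8% | 0.5% |
| 40% | 320 | 90 (45) | 32.5% | 11% |
| 45% | 284.4, so 285 | 101.25 (50.6) | 70.3% | 49% |

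**5. Allow for the per-arm requirement.** The same binomial model gives the total needed for a chosen chance that both arms reach 48:

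| Prevalence | 50% chance | 80% chance |
|---|---|---|
| 35% | 388 | 424 |
| 40% | 340 | 370 |
| 45% | 302 | 328 |

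**6. Find the attrition at which 300 would suffice in expectation.** Maximum attrition = 1 − 96 / (300p): 8.6% at 35%, 20% at 40% and 28.9% at 45%.

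**7. Compute power if recruitment did end at 300.** With m = 225p / 2 per arm, power = Φ(5 / (7.5√(2/m)) − 1.96).

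- 35%: m = 39.4, Φ(2.958 − 1.96) = 84%.
- 40%: m = 45, Φ(3.162 − 1.96) = 89%.
- 45%: m = 50.6, Φ(3.354 − 1.96) = 92%.

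The overall comparison would have 225 evaluable children against the 224 required.

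**The case against.** The strongest reply is that the trial is governed by counts and not by the forecast. Recruitment runs until both minimum counts are met, both counts are correct, and nothing in the article makes 300 a ceiling. This stands: if the rule is followed, the stated 90% power is not lost for either comparison. A reader might infer that the buckle comparison is underpowered. That would need recruitment to stop at 300, contrary to the rule, and even then power would be about 84–92%.

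Other parts of the reply also stand:

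- It would be too strong to say that 300 cannot deliver the buckle target. It is enough in expectation above 42.7% prevalence, or with lower attrition, and it could suffice by chance.
- It is tempting to say that 300 is just 224 inflated for attrition, so that prevalence was ignored. A midpoint-prevalence calculation also gives 300, so the origin of the figure is not established.
- A reader might infer harm to the timeline or budget. The article shows no budget, and its expected completion by 2023 (Trial status) is not linked to an accrual rate, so neither can be judged.
- The Abstract's 112 and 48 might be read as implying 42.9% prevalence. They are two minimum counts, and 42.9% lies inside the assumed range anyway.
- The protocol sets no assurance level, so the 80% totals only illustrate the effect of the per-arm rule.

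What does not stand is the defence that attrition is only approximate. At 40% prevalence a 20% loss would rescue the figure, but at 35% the loss would have to be 8.6% or less, which is not a rounding of 25%. The inflation by 1.25 does not cover the low end either: 275 × 1.25 = 343.75.

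**Conclusion.** The point holds as an inconsistency in the stated recruitment total. The sentence says that 300 allows for 25% attrition and for variation in buckle prevalence. On the section's own inputs it falls short in expectation over about three quarters of the assumed range, by 20 recruits at 40% and by 66 (22% of 300) at 35%. Even at 45%, the chance that both arms reach 48 is about one in two.

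The calculation assumes that attrition is 25% and equal in buckle and non-buckle children (the article gives no separate figure), that recruits split 150 per arm, and that prevalence is the same in both arms. The per-arm targets, the margin and the stopping rule are not in question. Because the rule is open-ended, the error concerns what the article forecasts and not the validity of the analysis. It should be fixed.

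**What to change.** Revise the last sentence of the Sample size section in one of these ways:

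- **If 300 is a forecast:** state that the overall target needs about 300 recruits at 25% attrition, and that the buckle target needs about 285 to 366 in expectation as prevalence falls from 45% to 35%. Add that requiring 48 in each arm pushes the total higher, for example to about 330–425 for an 80% chance that both arms get there.
- **If 300 is to be kept:** state the lower attrition or higher prevalence on which it rests, for example 20% attrition with 40% prevalence, or 25% attrition with at least 42.7%. These are break-even values in expectation only.
- **If 300 is in fact a cap:** say so, reconcile it with the open-ended rule, and report that the buckle comparison then has about 84%, 89% and 92% power at 35%, 40% and 45% prevalence.

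The Abstract needs no change. The cost is a reworded sentence and a less favourable headline total. The targets, the stopping rule and the analysis stay as they are.
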